**Methods:**

This trial is a multicenter, prospective randomized controlled clinical trial. We randomly allocated 144 participants to two groups of 72 patients. Patients in the treatment group were treated with QHN therapy. The control group had undergone insertion of acupuncture needles at sham acupoints not corresponded to acupuncture points. Participants in the verum treatment group and sham-acupuncture control group received 9 sessions over 6 weeks followed by 8 weeks of follow-up. The primary outcome was the change of motor function from baseline to weeks 6 and 14 measured by the PD Rating Scale-Part III Motor Examination (UPDRS-III). Secondary outcome measures included the change of PD daily quality of life-39 (PDQ-39) and Non-Motor Symptoms Scale for PD (NMSS) from baseline to weeks 6 and 14.

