### Trial Design

For this study, we designed a multicenter, assessor and statistician blinded, randomized controlled trial (RCT) to compare QHN therapy with sham acupuncture in patients with PD. Trials were conducted in three medical centers: the First Affiliated Hospital of Guangzhou University of Traditional Chinese Medicine, the Third Affiliated Hospital of Sun Yet-Sen University, and the Guangdong 999 Brain Hospital.

A total of 144 patients with PD were recruited and randomly assigned to either the QHN therapy group (treatment group) or sham-acupuncture group (control group) at a 1:1 ratio (Figure 1). Our study was conducted according to the Declaration of Helsinki, and the Standard Protocol Items: Recommendations for Interventional Trials (SPIRIT) checklist is given in Supplementary File 1.

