### Inclusion Criteria

The inclusion criteria in this study are as follows: (1) patients with PD, (2) patients of the age of 40–80 years old, (3) patients with a duration of PD of more than 1 year; (4) modified Hoehn-Yahr (HY) grades from 1 to 4; (5) patients who needed to take a stable dose of anti-PD drugs for more than 2 months, if treated with anti-PD drugs, or patients who had not received anti-PD medication for more than 2 months; (6) had clear consciousness and stable vital signs; and (7) patients who fully understood the study protocol and signed the consent form.

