### Sample-Size Calculation

This trial used a clinical-superiority design to verify that QHN therapy's effect was superior to that of sham acupuncture. The primary outcome measure was the UPDRS-III score difference before and after the treatment. According to previous research (17), assuming the standard deviation (SD) to be 8.0 and the mean of the treatment effect of the two groups to be 4.36 and 0.25, respectively, the statistical power was 80%, and the significance level was 0.05. Using PASS software requires each group to contain no <61 patients. With an estimated 15% dropout rate, we planned to recruit 72 patients for each group, for a total of 144 patients.

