### Statistical Analysis

We used mean and SD for normally distributed variables, or median (interquartile) for the variables not normally distributed, to summarize the participants' demographic, health conditions, and clinical outcomes at three different time points. Two statisticians, blinded to the group setting, analyzed the data independently *via* SPSS software (version 26.0). Missing data were imputed according to the last-observation-carried-forward (LOCF) principle. Furthermore, the data were analyzed by the intent-to-treat principle.

The normality of the variables was assessed using the normal probability plot. The continuous variables normally distributed were assessed by the student's t-test. Otherwise, the Mann-Whitney test or Wilcoxon test was applied. The Fisher's exact or the chi-square test was adopted for categorical data, and statistical significance was set at *p* < 0.05.

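### The primary comparison subtracts baseline UPDRS-III but does not adjust for it, which gives up some precision and leaves part of any chance baseline imbalance in the estimate

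*Protocol article*

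**What the plan says.** The Statistical Analysis section of the protocol article names the method: "The continuous variables normally distributed were assessed by the student's t-test". Mann-Whitney or Wilcoxon tests replace it when the normality plot is unfavourable. The section names no covariate, no ANCOVA or mixed model, and no term for centre. It does not say whether the test is run on change scores or on scores at each visit.

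Two other places define the primary outcome as a change. The Abstract (Methods) says "The primary outcome was the change of motor function from baseline to weeks 6 and 14", and Sample-Size Calculation says "The primary outcome measure was the UPDRS-III score difference before and after the treatment".

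Under Outcome Measurements, every scale is taken before treatment as well as at the two later visits, so a baseline value is planned for UPDRS-III, PDQ-39 and NMSS. Eligibility is broad: "modified Hoehn-Yahr (HY) grades from 1 to 4". On sites, Trial Design says "Trials were conducted in three medical centers". The section on randomization describes a central scheme and names no stratification factor.

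**The concern.** Subtracting baseline is a crude correction. It fixes the slope of follow-up on baseline at 1, whereas with equal variances the slope is r, which is below 1. This has two consequences.

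- The change score carries more variance than is left after regression on baseline, so the confidence interval is wider than it need be.
- If one arm starts worse by chance, regression to the mean makes it appear to improve more. A fraction (1 − r) of the imbalance then stays in the estimated treatment effect.

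No stratification on severity is described, so the article shows no protection in the design against such an imbalance. Adjustment would need no data beyond what is already planned, and it estimates the same mean difference between arms.

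**Working it through.** **Inputs from Sample-Size Calculation.** The SD comes from "assuming the standard deviation (SD) to be 8.0". It is read here as the SD of change, because it follows directly on the definition of the outcome as a before-after difference. The means come from "the mean of the treatment effect of the two groups to be 4.36 and 0.25, respectively", so the planned difference is 4.36 − 0.25 = 4.11. Alpha is 0.05, power 80%, with 61 per group, or 72 after 15% dropout.

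**Reproducing the plan's figure.** The two-sided normal formula, n = 2 × [8.0 × (1.960 + 0.842) / 4.11]², gives 59.5, rounded up to 60. The exact noncentral-t calculation gives 79.7% power at 60 per group and 80.4% at 61, so it requires 61. Then 61 / 0.85 = 71.8, rounded up to 72. A one-sided test would need only 47. The plan's numbers are therefore those of a two-sided, unadjusted t-test on the change score.

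**Effect of adjusting for baseline.** Let s be the SD of the raw score at each visit, assumed equal at baseline and follow-up, and r the correlation between them. The article does not give r.

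- Variance of change: 2s²(1 − r)
- ANCOVA residual variance: s²(1 − r²)
- Ratio: (1 + r)/2, so the saving is (1 − r)/2
- ANCOVA residual SD: 8.0 × √((1 + r)/2)
- Noncentrality at 61 per arm: 4.11 / (SD × √(2/61)), where √(2/61) = 0.181

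The one degree of freedom spent on the covariate is ignored.

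| Analysis | Variance saved | Residual SD | Noncentrality | Power at 61 per arm |
|---|---|---|---|---|
| t-test on change | – | 8.00 | 2.84 | 80.4% |
| ANCOVA, r = 0.5 | 25% | 6.93 | 3.28 | 90.1% |
| ANCOVA, r = 0.7 | 15% | 7.38 | 3.08 | 86.3% |
| ANCOVA, r = 0.8 | 10% | 7.59 | 2.99 | 84.3% |
| ANCOVA, r = 0.9 | 5% | 7.80 | 2.91 | 82.3% |

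**Effect of chance imbalance.** With the SD of change fixed at 8.0, the raw SD is s = 8.0 / √(2(1 − r)). The edge of the 95% range for the baseline difference at 61 per arm is 1.96 × s × √(2/61). The shift in the change-score estimate is (1 − r) times that difference.

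| r | Raw SD | Imbalance at 95% edge | Shift in estimate | Shift / 4.11 |
|---|---|---|---|---|
| 0.5 | 8.00 | 2.84 | 1.42 | 35% |
| 0.7 | 10.33 | 3.67 | 1.10 | 27% |
| 0.8 | 12.65 | 4.49 | 0.90 | 22% |
| 0.9 | 17.89 | 6.35 | 0.63 | 15% |

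ANCOVA removes this shift as far as the relation to baseline is linear.

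**Centre.** The article gives no centre effect. If centre explained an assumed 1% to 5% of the variance, power at 61 per arm would be 80.7% to 82.3%, against 80.4% without it.

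**The case against.** The strongest reply is that nothing is broken. A t-test on change is unbiased over randomisations, keeps its type I error, and is the test for which the trial was sized. The planned power is reached without adjustment. All of that stands. What is lost is efficiency, together with protection against an imbalance that happens to arise in this one trial.

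The gain may also be small. The broad range of disease stages suggests a wide spread of baseline scores. With the SD of change held at 8.0, a wide spread implies a high r: r = 0.5 needs a raw SD of only 8.0, whereas r = 0.9 corresponds to 17.9. The 90.1% figure is therefore the optimistic end, and a saving nearer 5% to 15% is easier to square with the eligibility criteria. This also stands.

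It can be said that a condensed article leaves covariates to an analysis plan. That plan is not shown and may adjust. But the article does name the test, and an adjusted primary analysis elsewhere would have to be reconciled with it.

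Three stronger readings are tempting, and the documents do not support them.

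- A reader might infer that baseline is ignored outright. Both definitions of the primary outcome are changes from baseline, so it is subtracted.
- A reader might infer that an imbalance enters the estimate in full. For a change score only (1 − r) of it does. A test on raw follow-up scores would carry r times the imbalance (1.4, 2.6, 3.6 and 5.7 points at r = 0.5, 0.7, 0.8 and 0.9). The Statistical Analysis section does not exclude such a test, but the outcome definitions point away from it.
- A reader might infer that three centres make the omission of centre an error. No stratification by centre and no centre effect are stated, so no design factor is shown to have been left out of the analysis.

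**Conclusion.** The point holds as a worthwhile improvement at almost no cost, and not as a defect in validity. The stated test is sound and meets its own power target. ANCOVA on baseline would save 5% to 25% of the variance for r from 0.9 down to 0.5, taking power at 61 per arm from 80.4% to between 82.3% and 90.1%. It would also remove a possible shift of about 0.6 to 1.4 points, which is not negligible beside a planned 4.11.

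These sizes rest on three assumptions: that 8.0 is the SD of change, that the variances at baseline and follow-up are equal, and that r lies in the range shown. The direction of the gain does not depend on the exact r. Under equal variances it is positive for any r below 1, apart from the one degree of freedom spent. Adjusting for centre is a minor extra.

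**What to change.** In Statistical Analysis, state that the primary analysis of UPDRS-III is an ANCOVA, or an equivalent repeated-measures model, with arm and baseline UPDRS-III. Fit it at each primary time point the protocol names (weeks 6 and 14), and report the adjusted mean difference with its 95% confidence interval. How the two time points share the primary claim is a separate question that this change does not settle.

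Use the matching baseline score for PDQ-39 and NMSS. Centre may be added as a covariate, with little gain expected. Keep the unadjusted t-test or rank test as a sensitivity analysis, so that the normality plot no longer decides the primary method. The treatment estimate from ANCOVA is the same whether follow-up or change is the dependent variable, so this wording also settles which score is analysed.

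The cost is a sentence or two in the analysis text, fixed before unblinding. It needs no new data, and the sample size should stay as it is.

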### Safety and Adverse Events (AEs)

Acupuncture is generally regarded as a safe therapy. Although AEs of acupuncture are rare, participants still may encounter hematoncus, dizziness, or fainting. If the above events occur, the acupuncture treatment will be stopped immediately, and the subject will be instructed to lie flat on the bed and drink warm water. AEs are caused by oral drugs that mainly include nausea, vomiting, dyspepsia, abdominal distension, orthostatic hypotension, hypohepatia, and renal function impairment. If these adverse reactions occur, participants will halt the use of medication, the respective alternative medicine, and symptomatic treatment as necessary. These AEs will be subcategorized by severity: mild, moderate, and severe AEs. For this study, mild AEs were defined as transient and tolerable AEs. Moderate AEs were defined as those that caused discomfort and potentially interfered with the subject's daily life. Severe AEs were defined as those that seriously affected the participants' physical health and even led to the risk of life. The details of AEs, such as time, duration, performance, measures to be taken, and the outcome, were recorded. The trial was stopped if there was an unacceptable risk of serious AEs in one or both treatment arms.

### Data Management and Monitoring

A case report form (CRF) was designed and utilized for data collection. The DMC recorded data information regarding subject demographics and assessment of patients. As necessary, the reason for patient dropout was documented in the CRF. At the end of the study, the investigator submitted all CRFs to the data management committee for review.

If more than 25% of the patients stopped treatment due to moderate or severe AEs, trial continuation would be required to be reassessed. The DMC was independently chaired by the Statistics Teaching and Research Office of Guangzhou University of Chinese Medicine and claimed to have no conflict of interest. The South China Research Center for Acupuncture and Moxibustion acted as an independent committee to monitor the progress and provide advice. The Ethics Committee of the First Affiliated Hospital of Guangzhou University of Chinese Medicine took part in endpoint adjudication.

For the duration of this study, the Project Management Group met every week to review trial conduct. Likewise, the Trial Steering Group met every month, and the independent Data Monitoring and Ethics Committee met every 6 months to review conduct throughout the trial period.

## Discussion

Previous investigations have investigated the efficacy of acupuncture for PD, with data supporting using these methods to benefit patients with PD (18, 19). Our findings from this study will further support our general understanding of therapeutic options and elucidate the benefits of QHN therapy in terms of improving motor symptoms, such as postural instability and functional mobility. If identified that it effectively alleviates motor symptoms and improves HRQoL, it could serve as a low-cost adjuvant therapy for patients with PD with motor symptoms.

This research will also evaluate the efficacy of QHN therapy for non-motor symptoms of PD, such as chronic constipation and insomnia. In addition, we aimed to explore alterations in regional brain activity before and after therapy through Functional brain imaging techniques.

*Qihuang Needling* therapy adopts a tailored disposable sterile needle characterized by its arc-shaped pinpoint, hollow-stiff needle body, and transparent handle. Compared with ordinary traditional manual acupuncture (TMA), the advantages of QHN therapy are that it provides a stronger *Deqi* sensation at the acupoint, reduces puncture pain, and has shorter operation times. Furthermore, it is regarded as safer than TMA because an acupuncturist could identify bleeding directly through a transparent handle to avoid damage to blood vessels. In support of these benefits, previous trials have shown that the efficacy of QHN therapy for musculoskeletal diseases is superior to TMA (20–23).

Several studies have demonstrated that acupuncture is widely used for Chinese patients with PD (7). Additionally, our previous clinical observation indicates that QHN therapy may have sustained effects, which may be superior to other acupuncture approaches. However, evidence for the therapeutic effects of acupuncture is limited. A review study summarizing 35 investigations in mainland China, Japan, Korea, Taiwan, and the United States of America demonstrated that most of these trials had small sample sizes, and some were individual case reports (10). Additionally, many studies are limited by methodological approaches, such as the lack of a placebo control group and/or deficiencies in their randomized design. To further elucidate QHM efficacy and address these previous research limitations, this research uses a multicenter, randomized, placebo-controlled trial with 400+ subjects to provide advantages in methodological design.

### Limitations

Our study has several recognized limitations. Firstly, it is an open-label research investigation due to the inability of blind acupuncturists. Despite blinding assessments being performed, we did not control for patients' and acupuncturists' expectations of efficacy, which may alter the results of the blinding assessment and the effects of QHN therapy. Secondly, the longer-term follow-up has not been well assessed because PD is a chronic and progressive condition. Thirdly, limited by the expenditure, gait examination will not be performed in patients with PD. Therefore, future clinical trials may need to include taking gait examination as the primary outcome, and a comparison to standard care and a waiting list.

## Trial Status

This protocol is version 2.0. 2019-03-17. The participants will be recruited from 1 March 2022 to 1 June 2023.

## Ethics Statement

The studies involving human participants were reviewed and approved by the Ethics Committee of the Guangzhou University of Traditional Chinese Medicine (Guangzhou, China) in July 2019 (K2019-007). Written informed consent will be obtained from eligible participants before any assessment or intervention.

## Abbreviations

PD: Parkinson's Disease
QHN: Qihuang Needling
RCT: Randomized controlled trial
AEs: Adverse events
CRF: Case report form
HY: Hoehn-Yahr
DMC: Data Monitoring Committee
UPDRS-III: Parkinson's Disease Rating Scale-Part III
PDQ-39: Parkinson disease daily quality of life-39
NMSS: Non-Motor Symptoms Scale for Parkinson's disease
SD: standard deviation
AEs: adverse events.
